# Simvastatin to modify neutrophil function in older patients with septic pneumonia (SNOOPI): study protocol for a randomised placebo-controlled trial

**DOI:** 10.1186/1745-6215-15-332

**Published:** 2014-08-22

**Keywords:** Neutrophils, Sepsis, Pneumonia, Simvastatin, Healthy Ageing

## Abstract

**Background:**

Community-acquired pneumonia (CAP) is considered the leading cause of death from infectious disease in developed countries, while complications of CAP - sepsis being the most common and challenging - increase the risk of mortality. During the progression of sepsis, a state of neutrophil ‘paralysis’ develops resulting in the impairment of neutrophil anti-microbial functions including: chemotaxis, production of reactive oxygen species, and formation of neutrophil extracellular traps (NETs). Mechanisms underlying defective neutrophil function remain elusive although NET formation has been implicated in the immunosuppression and increased rates of sepsis observed in neonates. There is, however, increasing evidence that statins are able to modulate neutrophil function in sepsis as several systematic reviews have concluded that statins have a role in improving infection-related outcomes and mortality while, *in vitro*, statins have also been shown to boost NET formation in healthy individuals.

**Methods/design:**

The ‘SNOOPI’ trial is a phase 4, randomised placebo-controlled trial. The aim of this study is to determine whether oral treatment with simvastatin compared to placebo optimises neutrophil anti-microbial functions in elderly patients with septic pneumonia improving patient outcomes in the elderly. The primary outcome will be NET production within 72 to 96 hours of treatment with simvastatin or placebo measured in response to a number of inflammatory mediators, including IL8, f-Met-Leu-Phe and lipopolysaccharide. Secondary outcomes include neutrophil migratory capacity; reactive oxygen species production; neutrophil phagocytic capacity; safety and tolerability of simvastatin administration within this patient group; biological markers of neutrophil activation, the inflammatory response, alveolar epithelial and endothelial injury; systemic endothelial function biomarkers and pulmonary extracellular matrix degradation. This study aims to recruit 60 patients admitted into Queen Elizabeth Hospital Birmingham NHS-Foundation Trust.

**Discussion:**

This study will investigate the ability of *in vivo* simvastatin therapy to modulate neutrophil anti-microbial functions in CAP-associated sepsis.

**Trial registration:**

EudraCT number: 2012-003343-29 (Trial Registered: 26 November 2012).

**Electronic supplementary material:**

The online version of this article (doi:10.1186/1745-6215-15-332) contains supplementary material, which is available to authorized users.

## Background

Community-acquired pneumonia (CAP) is considered the leading cause of death from infectious disease in developed countries. Increased mortality is associated with systemic manifestations and complications of CAP, with sepsis being the most common and challenging. The incidence of sepsis increases with age, while age is also a predictor of outcome in patients with pneumonia
[1].

Sepsis is characterised by a state of systemic immune dysregulation and coagulopathy produced by invasive microorganisms and/or their microbial products, such as lipopolysaccharide (LPS). The initial cytokine storm and systemic inflammatory response syndrome (SIRS) is followed by a compensatory anti-inflammatory response which leads to a state of significant immuno-paralysis. This has been implicated in the progression of sepsis and subsequent development of acute lung injury (ALI), multi-organ dysfunction (MODS) and death
[2, 3].

Neutrophils constitute our main immune defence against microbial infection by rapidly migrating to sites of infection and/or inflammation. In a process known as chemotaxis, neutrophils are able to sense and subsequently respond to shallow gradients of chemoattractants formed of chemotactic peptides, including cytokines, bacterial products and complement proteins
[4]. Once at the site of infection, neutrophils act to eliminate any foreign material in an effort to prevent widespread tissue damage and ultimately resolve infection. During the progression of sepsis, a state of neutrophil ‘paralysis’ develops resulting in the impairment of neutrophil anti-microbial functions including: chemotaxis, production of reactive oxygen species (ROS), and formation of neutrophil extracellular traps (NETs)
[5]. Unable to contain the infection, widespread dissemination of pathogenic material occurs throughout the host, augmenting inflammation and leading to the development of ALI and MODS
[6]. Secondary to the development of ALI and MODS, this immune paralysis or chronic immunosuppression leads to an increased risk of secondary infections further exacerbating the increased risk of mortality.

Mechanisms underlying defective neutrophil function remain elusive although NET formation has been implicated in the immunosuppression and increased rates of sepsis seen in neonates
[7], while other studies suggest NETs may exaggerate endothelial damage
[8, 9]. The term NETs refers to the formation of extracellular fibres composed of de-condensed chromatin laden with anti-microbial proteins. Although phenotypically and functionally distinct from apoptosis, ‘NETosis’ does result in cell death; however, this allows neutrophils to exert their anti-microbial functions beyond their typical lifespan
[10].

To date, there are no studies that specifically look at NET formation in CAP-associated sepsis. There is, however, increasing evidence that statins are able to modulate neutrophil function in sepsis with a recent study demonstrating the ability of statins to reduce the neutrophil infiltrate following LPS challenge in bronchoalveolar lavage fluid taken from patients receiving simvastatin prior to challenge
[11]. Furthermore, the reduction in neutrophil counts was not associated with a decrease in pro-inflammatory mediator expression, suggesting it reflects a reduced neutrophil response or increased neutrophil apoptosis
[11]. Statins inhibit 3-hydroxy-3 methylglutaryl coenzyme A reductase, a rate-limiting enzyme in the biosynthesis of cholesterol, and have been shown to exert numerous effects in addition to their lipid-lowering properties including potentially anti-inflammatory and immunomodulatory effects
[1]. Several systematic reviews have concluded that statins have a role in improving infection-related outcomes and mortality; however, most of this evidence is limited to retrospective and prospective observational studies
[12, 13]. *In vitro*, statins have also been shown to boost NET formation in healthy individuals with the consequent elimination of bacteria - an effect which could therefore be an important determinant of outcome in patients with CAP-associated sepsis
[14].

### Impaired neutrophil chemotaxis in the elderly

Neutrophils from healthy elderly donors demonstrate features of immune-paralysis that resemble those seen in patients with sepsis: healthy elderly patients (over 60 years) demonstrate defective directional migration (chemotaxis) and overall accuracy (chemotactic index) whilst maintaining their speed of migration (chemokinesis) when migrating towards IL8 and the bacterial protein f-Met-Leu-Phe (fMLP)
[15].

### Statins and sepsis

The ASEPSIS trial, a phase II randomised controlled trial, demonstrated that acute administration of atorvastatin reduces the progression of sepsis to severe sepsis
[16]. These changes were not associated with systemic levels of cytokines or chemokines in contrast to other reported studies suggesting the cellular effects of statins may be more important than modulation of systemic mediators.

### Community-acquired pneumonia-associated sepsis and neutrophil extracellular traps

During the early stages of CAP-associated sepsis, NET production is suppressed with improvements occurring during resolution. In addition, NET release was significantly lower in CAP patients who meet the criteria for severe sepsis. Taken together these data suggest that neutrophil function is a feature of CAP-associated sepsis, especially in the elderly, and that statin therapy may have potential to restore the defects in these neutrophils both *in vivo* and *in vitro*.

In light of these data, we hypothesise that the increased incidence and poorer outcomes observed in the elderly population in relation to pneumonia and sepsis may be due to defective neutrophil function, and that restoration of these functions may therefore improve outcome, especially in the elderly. The SNOOPI trial therefore aims to determine whether oral treatment with simvastatin optimises neutrophil anti-microbial functions in elderly patients admitted into Queen Elizabeth Hospital Birmingham (QEHB) with septic pneumonia, improving patient outcomes in the elderly. Alterations in neutrophil function will be related to clinical outcome, disease-relevant severity scores and biomarkers present in blood and urine.

## Methods/design

### Trial approvals and conduct

The trial is approved by Yorkshire and Humber Ethics Committee (REC 12/YH/0375) and is registered on the European Clinical Trials Database (EudraCT Number: 2012-003343-29). The trial sponsor is the University of Birmingham (Reference: RG_12-179). The trial is funded by the British Lung Foundation (BLF reference LT/12) and will be carried out in accordance with the principles of the International Conference on Harmonisation Good Clinical Practice guidelines, applicable UK legislation and standard operating procedures of the Respiratory Research Group at the University of Birmingham. Results of the trial will be reported in accordance with consolidated Standards of Reporting Trials 2010 guidelines
[17].

### Outcome measures

#### Primary outcome

The primary outcome will be NET production within 72 to 96 hours of treatment with simvastatin or placebo, measured in response to a number of inflammatory mediators including IL8, fMLP and LPS and using phorbol-12-myristate-13-acetate as a positive control
[18] (for full methods, see Additional file
1).

#### Secondary outcomes

Secondary outcomes of this trial include parameters describing neutrophil migratory capacity; ROS production; neutrophil phagocytic capacity; safety and tolerability of simvastatin administration within this patient group; biological markers of neutrophil activation (for example, myeloperoxidase), the inflammatory response (for example, IL6), alveolar epithelial and endothelial injury (for example, von Willebrand factor), and systemic endothelial function biomarkers (for example, albumin:creatinine ratio); pulmonary extracellular matrix (ECM) degradation and turnover of peptide; and, finally, the relationship of baseline and changes in parameters described above to clinical relevant outcomes (survival, development of organ failure, admission onto intensive therapy unit, sequential organ failure assessment score, ventilator-free days and muscle wastage during the inpatient stay). These assessments will be made at baseline, on days 4 and 7, and in convalescent samples.

Neutrophil migratory capacity will be measured using a modified Dunn chamber as described previously
[15, 19]; neutrophil ROS production will be measured using a luminol-based assay and phagocytic capacity measured by flow cytometry. Plasma indices of neutrophil activation, the inflammatory response and alveolar epithelial and endothelial injury will be measured by enzyme-linked immunosorbent assay, and systemic endothelial function biomarkers and pulmonary ECM degradation will be measured in urine collected from an indwelling urinary catheter (for full methods, see Additional file
1). These assessments will be made at baseline, on days 4 and 7, and in convalescent samples (≥6 weeks post-discharge).

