### Eligibility criteria

Patients will be eligible for the trial if they fulfil the following criteria:

Aged over 60 years.Meet the British Thoracic Society guidelines for diagnosis of CAP, namely symptoms and signs consistent with an acute lower respiratory tract infection associated with radiographic shadowing for which there is no other explanation
[20]. Signs and symptoms include three or more of the following: cough, sputum production, breathlessness, pleuritic chest pain, haemoptysis, fever, headache, signs consistent with pneumonia on chest auscultation.CAP patients will also need to meet the criteria for sepsis based on the standard definitions as published in the 2008 Surviving Sepsis Campaign Guidelines [21] as illustrated in Table  1.All sepsis and pneumonia criteria must occur within the same 24-hour period (sepsis is defined as evidence of infection plus SIRS; see Table 2).Patients must be enrolled within 48 hours of admission to hospital.

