### Trial conduct

#### Approach to patients and obtaining informed consent

Patients will be identified on the daily consultant ward rounds that take place on the 40-bed clinical decision unit and 80-bed ICU at the QEHB (approximately 60 to 70 daily admissions). Eligible patients may only be included in the trial after obtaining written informed consent.

Where necessary, informed consent may be sought from the patient’s personal legal representative who may be a relative or close friend. If the patient is unable to give informed consent and no personal legal representative is immediately available, a senior doctor (consultant or registrar) who is not connected with the trial may act as professional legal representative.

A copy of the signed informed consent form will be placed in the patients’ medical records and the originals will be retained by the personal legal representative and by the Principal Investigator in the investigator site file.

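### Urine for two secondary outcome groups is to come from an indwelling catheter, a source that does not fit the planned sampling schedule, least of all at convalescence

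*Protocol article*

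**What the plan says.** All the sampling text is in the protocol article, under Secondary outcomes. It gives one source for two groups of markers, the endothelial function markers and those of matrix degradation: "pulmonary ECM degradation will be measured in urine collected from an indwelling urinary catheter", with the endothelial markers named in the same sentence. The endothelial group is illustrated earlier in the section as "systemic endothelial function biomarkers (for example, albumin:creatinine ratio". The sentence ends by referring the reader to Additional file 1 for full methods. The schedule follows directly: "These assessments will be made at baseline, on days 4 and 7, and in convalescent samples (≥6 weeks post-discharge". No outcome is exempted, and the article does not mention voided urine.

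Other sections bear on who will have a catheter:

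- Under Eligibility criteria, entry needs community-acquired pneumonia with sepsis, where "sepsis is defined as evidence of infection plus SIRS". Severe sepsis is not required. Neither the inclusion nor the exclusion list mentions a catheter.
- Under Approach to patients and obtaining informed consent, patients are identified on the "40-bed clinical decision unit and 80-bed ICU at the QEHB".
- Under Administration of investigational medicinal product, treatment may end before 7 days because the patient has been discharged.
- Under Statistical analysis plan, the treatment effect is to be analysed by intention to treat.

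**The concern.** The stated source and the stated schedule do not fit together. A patient seen at least 6 weeks after discharge will rarely have an indwelling catheter. During admission, the sample exists only if the patient has a catheter on that day, and the trial neither requires nor assigns one.

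Three things are at stake.

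- **Comparison of arms.** Whether a patient still has a catheter on day 4 or day 7 depends on the clinical course after randomisation, which the trial hypothesises that simvastatin may improve. Comparing arms among patients with catheter urine conditions on a post-randomisation state, and this sits badly with the intention-to-treat aim.
- **Relation to clinical outcomes.** The section also plans to relate baseline values and changes in the markers to survival, organ failure, intensive therapy admission and organ failure score. If having urine data is itself tied to severity, those associations come from a selected sample. A change from baseline needs urine at both times.
- **Recovery value.** Without convalescent urine there is no within-patient reference for these markers.

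**Working it through.** **1. The plan's own figures.** The only sample sizes derived in the article are for functional measures, chiefly NET production; none is given for urine markers. For NET production, a difference of 5,000 AU with the day 4 SD of 5,100 AU is a standardised difference of 5,000 / 5,100 = 0.98. A two-sample t-test at two-sided 0.05 needs 17.35 per arm for 80% power and 22.87 for 90%. These round up to the stated 18 and 23, so the primary sample size is not in question.

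**2. Source against schedule.**

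| Time | Condition for a catheter sample | What the article provides |
|---|---|---|
| Baseline | Catheter in place at entry | Not an entry criterion; entry possible without severe sepsis and from the clinical decision unit |
| Days 4 and 7 | Still an inpatient with a catheter | Catheter not assigned by the trial; discharge before day 7 foreseen |
| At least 6 weeks after discharge | Catheter in place after discharge | No alternative source stated |

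The last row is the clearest mismatch. The middle row is where the comparison of arms is affected.

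**3. Precision, for illustration.** The documents give no catheterisation rate, so the fraction *f* of patients with catheter urine is assumed. With the same SD and an equal split between arms, the standard error of a difference in means is multiplied by √(1/*f*).

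- *f* = 0.6: 0.6 × 60 = 36 patients; √(1/0.6) = 1.29.
- *f* = 0.3: 0.3 × 60 = 18 patients; √(1/0.3) = 1.83.

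The same loss can be shown as the standardised difference detectable with 80% power (t-test, two-sided 0.05), starting from 30 recruited per arm:

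| Assumed fraction with urine | Per arm | Detectable difference (SD units) |
|---|---|---|
| 100% | 30 | 0.74 |
| 75% | 22.5 | 0.85 |
| 50% | 15 | 1.06 |
| 25% | 7.5 | 1.57 |

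These figures show how the loss grows with the assumed fraction. They do not estimate that fraction.

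**4. Bias.** No figure can be given. Bias in the comparison of arms requires that treatment, directly or through recovery, affects who still has a catheter. If it does not, the cost is lower precision and a narrower population.

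**The case against.** The strongest objection is Additional file 1. The catheter sentence refers to it for full methods, and collection details are what an article leaves to a supplement. That file may allow voided urine. This stands as a limit on the conclusion but does not remove the point: the article does not leave the source open, but names one and then sets a schedule that this source cannot generally serve.

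The schedule wording is also generic. A near-identical sentence earlier in the section follows a list that includes survival and ventilator-free days, which are not measured in convalescent samples. It may therefore be a loose summary rather than a firm commitment to urine at 6 weeks or more. That is fair, but the later sentence follows directly on the assay descriptions and exempts no marker.

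A reader might go further and infer that urine will exist only in the sickest patients, that the convalescent assessment is impossible, or that bias is established. The documents support none of these. They do not use the word only for the catheter source. They give no catheterisation rate, no indications for catheters and no recruitment split between the decision unit and the ICU, and some older patients have catheters for reasons other than acute severity. An effect of simvastatin on catheter status within 4 to 7 days is plausible but not shown.

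**Conclusion.** The point holds in a limited form. The article states a urine source that does not fit its own schedule. Followed as written, the endothelial and extracellular matrix markers would be observed mainly in catheterised, probably sicker, patients, and almost never at convalescence. The day 4 and day 7 comparisons would then lose precision and could carry selection bias.

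The loss of precision depends wholly on an unstated rate: a factor of about 1.3 to 1.8 in the standard error under the assumed range of 30% to 60%. The size of any bias is unknown. The primary outcome and its sample size are unaffected, so this is a correction that should be made rather than a threat to the trial's main result. It is also subject to what Additional file 1 says.

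**What to change.** First check Additional file 1. If it already allows another source, reconcile the article and the file. If it does not, amend the Secondary outcomes text to say:

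- urine is taken from a catheter where one is already present and otherwise as a voided spot sample;
- this applies to all randomised patients at every scheduled time point, including convalescence;
- urine markers are normalised to creatinine, as the albumin:creatinine ratio already is;
- the collection method is recorded for each sample, with a sensitivity analysis by method.

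If voided samples cannot be taken, the alternative is to limit the urine outcomes to the patients and times for which catheter urine exists, describe them as such, and state how missing values are handled.

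The amendment is short. Its cost is some added variability from mixed collection methods. It also cannot recover the past: according to Trial status, recruitment began in December 2013, so urine not taken from patients already enrolled is lost, and those patients will have been sampled under a different rule.

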### Eligibility criteria

Patients will be eligible for the trial if they fulfil the following criteria:

Aged over 60 years.Meet the British Thoracic Society guidelines for diagnosis of CAP, namely symptoms and signs consistent with an acute lower respiratory tract infection associated with radiographic shadowing for which there is no other explanation
[20]. Signs and symptoms include three or more of the following: cough, sputum production, breathlessness, pleuritic chest pain, haemoptysis, fever, headache, signs consistent with pneumonia on chest auscultation.CAP patients will also need to meet the criteria for sepsis based on the standard definitions as published in the 2008 Surviving Sepsis Campaign Guidelines [21] as illustrated in Table  1.All sepsis and pneumonia criteria must occur within the same 24-hour period (sepsis is defined as evidence of infection plus SIRS; see Table 2).Patients must be enrolled within 48 hours of admission to hospital.

**Table 1 Tab1:** **Surviving Sepsis Campaign Guideline definitions of sepsis**

Condition	Definition
Sepsis	SIRS plus new-suspected infection
Severe sepsis	Sepsis plus sepsis-induced organ dysfunction
Organ dysfunction	Sepsis-induced hypotension
	Lactate > normal laboratory results
	Urine output <0.5 mL/kg/hour for >2 hours despite adequate fluid resuscitation
	ALI with PaO_2_/FiO_2_ < 250 in the absence of pneumonia as infection source
	ALI with PaO_2_/FiO_2_ < 200 in the presence of pneumonia as infection source
	Creatinine >176.8 mmol/L
	Bilirubin >34.2 mmol/L
	Platelet count >100,000/mm^3^
	Coagulopathy (INR >1.5)
Septic shock	Severe sepsis plus hypotension not reversed by fluid resuscitation

ALI, acute lung injury; FiO_2_, fraction of inspired oxygen; INR, International normalised ratio; PaO_2_, partial pressure of oxygen in blood; SIRS, systemic inflammatory response syndrome.

